#### Analysis of secondary endpoints

All secondary outcomes will be evaluated descriptively. Analyses of secondary endpoints will be conducted based on the m-ITT set, with additional sensitivity analyses based on the PP set.

The secondary endpoints “Deep incisional and/or organ or space SSI within 90 days after surgery” and the secondary endpoint “systemic infections” will be evaluated by means of a logistic mixed regression model using for the fixed factors treatment group and location, as well as the random factor centre. Odds ratios will be given with 95% confidence intervals together with descriptive *p* values.

The secondary endpoint LOS will be assessed using Kaplan-Meier estimates for each treatment group. A Cox regression frailty model with the fixed factors treatment group and location and the random factor centre will be fitted. A hazard ratio for the factor treatment group will be given with a 95% confidence interval together with a descriptive *p* value.

HRQoL at follow-up will be analysed using a linear mixed model for repeated measurements, taking into account the HRQoL baseline value, treatment group, and location as fixed factors, centre as random factor, and time as repeated factor using an unstructured covariance matrix. 95% confidence for the mean difference between treatment groups will be given with descriptive *p* values. No imputation of missing data will be done for secondary endpoints.

Furthermore, the treatment effect will be assessed descriptively within several subgroups of interest to identify potential prognostic and predictive factors.

The safety analysis includes calculation of frequencies and rates of adverse and serious adverse events together with 95% Wilson-type confidence intervals. Safety analysis will be based on the safety set comprising all subjects of the m-ITT set who postoperatively received at least one dose of placebo or postoperative AP and will allocate the subjects to the treatment they actually received, regardless of randomisation.

Statistical analysis is based on the International Conference on Harmonization (ICH) Guidelines “Structure and Content of Clinical Study Reports” and “Statistical Principles for Clinical Trials” [28]. All statistical procedures are done according to the current standard operating procedures (SOPs) of the Institute of Medical Biometry and Informatics, University of Heidelberg (IMBI).

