## Methods: participants, interventions, and outcomes

### Study setting {9}

The clinical trial will be conducted on a national multicentre basis. Recruitment and treatment will take place at 14 experienced centres. Detail lists of study sites can be obtained at the registration form German Clinical Trials Register - DRKS00022838.

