### Secondary endpoints

Deep incisional and/or organ or space SSI as defined by CDC/KISS [17, 21] 30 (POD30) to 90 days after surgery (POD90). As an implant is used, a deep incisional or organ and space SSI may occur within 90 days after surgery according to CDC/KISS criteria [17, 21].Systemic infections, defined as a systemic inflammatory response syndrome associated with a postoperative SSI consecutive to OS. Systemic infections might be associated with postoperative SSI. However, since OS is a scheduled procedure, and surgeons do not perform it in patients at high risk of infection, systemic infection is very unlikely to occur.Length of hospital stay (LOS), defined as the number of days from OS to the day of discharge. LOS is an important subject-oriented outcome and can be directly or indirectly influenced by SSI.Health-related quality of life (HRQoL), measured by SF-36 and OHIP-G-14 [22–24]. HRQoL is an important patient-oriented outcome and can be directly or indirectly influenced by SSI. Furthermore, there might be connections between subjects’ expectations regarding the postoperative AP and their QoL independent from an SSI. Antibiotics are often prescribed due to subjects’ expectations in order to enhance their QoL.Non-severe medication related adverse events (AE), defined as mild diarrhoea or skin rash due to antibiotic administrations. Ampicillin/Sulbactam antibiotic are well established, tested and tolerated antibiotics. However, diarrhoea and skin rashes are reported. Adverse effects associated with antibiotic intake are of great interest when evaluating the elective/prophylactic use of antibiotics.

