### Sample size {14}

The sample size calculation is based on the primary efficacy endpoint “Occurrence of SSI within thirty days after surgery (V4)”. A recent meta-analysis [1] reported a pooled risk ratio of 0.42 (95% confidence interval: [0.24; 0.74]) for the comparison of long-term (before or during surgery and longer than one day after surgery) versus short-term (before or during surgery and/or during the same day) antibiotic prophylaxis. Furthermore, pooled event rates of 7.1% for long-term and 16.8% for short-term antibiotic prophylaxis were observed, yielding a difference of 9.7%. Thus, for both the AP and no AP group, an infection rate of 7.1% is expected, as the assumption of equal rates is the standard approach for a power calculation in non-inferiority trials. If the rate in the no AP group is at most 4% higher than the rate in the AP group, this will be considered as clinically irrelevant since possible SSI might have an increase in clinically manageable morbidity, however, no life-threatening consequences for subjects.

Based on these assumptions, a total of *n* = 1346 subjects (673 per group) are required to demonstrate non-inferiority at a margin of *δ* = 4% for no AP as compared to AP applying the Farrington-Manning test at a one-sided significance level of *α* = 2.5% with a power of 1-β = 80% (calculations performed with ADDPLAN v6.1). The adjustment for the factor centre using a Mantel-Haenszel type test is expected to yield an additional increase in power. To account for a drop-out-rate of 5%, a total of *n* = 1420 subjects (710 per group) will be randomised.

The potential problem of missing values for the primary outcome due to loss to follow up or premature withdrawal from the study before the measurement of the primary endpoint will be partly resolved in the confirmatory analysis by application of a pre-defined imputation strategy (see the “Statistical methods” section).

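### Systemic infection, which the protocol expects to be very rare, is assigned a mixed logistic model whose treatment odds ratio may well have no finite estimate

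*Protocol article*

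**What the plan says.** The protocol article, under Secondary endpoints, specifies systemic infection as "defined as a systemic inflammatory response syndrome associated with a postoperative SSI consecutive to OS". Every case must therefore accompany an SSI. The same item adds that "systemic infection is very unlikely to occur", because the surgery is elective and is not done in patients at high risk of infection. No numerical rate is given.

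Under Analysis of secondary endpoints, systemic infection is paired with deep incisional or organ/space SSI. Both "will be evaluated by means of a logistic mixed regression model using for the fixed factors treatment group and location", plus centre as a random factor. The output is fixed too: "Odds ratios will be given with 95% confidence intervals together with descriptive" p values. The section opens with the statement "All secondary outcomes will be evaluated descriptively". It places the main analysis in the modified ITT set, adds a per-protocol sensitivity analysis, and rules out imputation for secondary endpoints.

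Three other facts matter here. The random factor has 14 levels (Study setting: "Recruitment and treatment will take place at 14 experienced centres"). The Sample size section requires 673 evaluable subjects per group and randomises 710 per group. For the primary endpoint it states that "for both the AP and no AP group, an infection rate of 7.1% is expected".

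**The concern.** A logistic model estimates a log odds for each arm. If an arm has no event, its log odds runs off to minus infinity. The treatment odds ratio is then zero or infinite, or undefined if both arms are empty, and a Wald interval around it means nothing. The random centre effect does not cure this, and a variance across 14 centres can hardly be estimated from a handful of events.

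The protocol expects very few events and still names this model and this output. What is at stake is the usefulness of one secondary result. The Sample size section defends the 4% margin partly on the ground that extra SSIs would not be life-threatening, and systemic infection is the listed secondary endpoint that bears most directly on that premise. Very few events, or none, would be reassuring in absolute terms, but an odds ratio that cannot be estimated does not convey this.

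**Working it through.** **Inputs.** From the protocol: 673 evaluable and 710 randomised per arm, 1:1 allocation, 14 centres, SSI rate 7.1% in both arms, margin 4 percentage points, one-sided alpha 2.5%, power 80%. Assumed, because the protocol gives none: a systemic infection rate p, equal in both arms, ranging from 0.05% to 1%.

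**Step 1: the plan's own arm size.** The Farrington-Manning formula is n = [(z₀.₉₇₅·s₀ + z₀.₈₀·s₁)/δ]². The restricted estimates under the null are 0.0959 and 0.0559.
- s₀ = √(0.0959·0.9041 + 0.0559·0.9441) = 0.3734
- s₁ = √(2·0.071·0.929) = 0.3632
- n = [(1.960·0.3734 + 0.8416·0.3632)/0.04]² = 672.8, so 673 per arm and 1346 in total

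The stated figure is reproduced. It is used here only to fix the arm size.

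**Step 2: chance that an arm is empty.** Let q = (1−p)ⁿ be the probability of no event in one arm. Then P(at least one arm empty) = 2q − q², and P(no event in the trial) = q². Example at p = 0.1% and n = 673: q = 0.999⁶⁷³ = 0.510, and 2·0.510 − 0.510² = 0.760.

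| Assumed rate p | Expected events in total, n = 673 | At least one arm empty, n = 673 | No event at all, n = 673 | At least one arm empty, n = 710 |
|---|---|---|---|---|
| 0.05% | 0.7 | 92% | 51% | 91% |
| 0.1% | 1.3 | 76% | 26% | 74% |
| 0.2% | 2.7 | 45% | 7% | 42% |
| 0.3% | 4.0 | 25% | 2% | 22% |
| 0.5% | 6.7 | 7% | 0.1% | 6% |
| 1% | 13.5 | 0.2% | <0.1% | 0.2% |

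With 673 per arm, the probability is 50% at p = 0.18% (about 2.5 events in total) and 5% at p = 0.54% (about 7.3 events).

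**Step 3: the same check as a share of SSI.** Because a case requires an SSI, p can be written as an assumed share of 7.1%. The chance of at least one empty arm is 86% if 1% of SSI cases become systemic (p = 0.071%), 62% at 2%, 17% at 5% and 1.7% at 10%.

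**Step 4: location.** The share of mandibular-only procedures is not stated, so 20% to 50% is assumed. In a simulation of 200,000 trials per setting, at least one arm or one location stratum had no event in 84–90% of trials at p = 0.1%, 58–71% at 0.2% and 11–29% at 0.5%. An empty location sends only the location coefficient to infinity. The treatment odds ratio can remain finite, though the fit may not converge.

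**Step 5: what an absolute measure gives.** With 0/673 in an arm, the exact two-sided 95% upper limit for that arm's rate is 1 − 0.025^(1/673) = 0.55%. With 0/673 in both arms, the Miettinen-Nurminen limits ±d solve d² = 1.96²·[d(1−d)/673]·(1346/1345). This gives d/(1−d) = 0.00571 and limits of ±0.57 percentage points. The between-arm contrast therefore has a finite interval even in the most extreme case.

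**The case against.** The strongest objection is that this belongs to the SAP. The section on additional analyses leaves detailed methodology to that document, which is not shown and may contain a rule for sparse events. This is right as far as it goes, so a missing fallback is no finding. The point that stands is narrower: the protocol itself names the model and the output for an endpoint that it expects hardly ever to occur.

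Second, no event rate is given, so how often the model would fail is conditional. This stands. From about 0.5% upwards an empty arm is uncommon, and a reader who takes the protocol to prove that the odds ratio will usually fail goes beyond the text.

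Third, the endpoint is descriptive, counts would survive a failed model, and the safety analysis plans Wilson-type intervals for adverse-event rates. The first two parts stand and limit the importance. The Wilson intervals help only partly: they describe adverse-event rates by treatment received and give no between-arm contrast for this endpoint.

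Two stronger readings are also tempting. One is that an empty location stratum also destroys the treatment odds ratio, which Step 4 shows is not so. The other is that deep or organ/space SSI, analysed with the same model, shares the defect. The protocol does not call that endpoint unlikely, and nothing in it supports an event threshold for switching method there.

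**Conclusion.** The point holds for systemic infections, as a modest one. The model and output that the protocol prescribes fit its own expectation badly. At rates up to about 0.2–0.3%, a fair reading of very unlikely, the chance that no finite treatment odds ratio exists runs from about one in four upwards. At 0.5% it falls to about 7%, and at 1% it is negligible. Even at 0.5%, about 7 events are little for an intercept, two fixed effects and a centre variance.

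These figures assume equal rates in both arms and 673 evaluable subjects per arm; 710 per arm changes them by at most about 3 percentage points. For a given no-AP rate, a lower rate under AP would make an empty AP arm more likely. The per-protocol and subgroup analyses would usually have fewer events still.

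The primary non-inferiority conclusion is not affected.

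**What to change.** For systemic infections only, replace the mixed logistic model as the main analysis. Report the number of events and the rate per arm, and the risk difference (no AP minus AP) with a two-sided Miettinen-Nurminen 95% interval. This interval exists with zero events in one or both arms, and it is on the same absolute scale as the primary analysis. If an odds ratio is also wanted, report it as supportive, from a Firth-penalised logistic regression with treatment group and location and without the random centre effect. Leave the planned model for deep or organ/space SSI as it is.

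The change needs a few lines in the SAP, settled before unblinding so that the method is not chosen after a model has failed. It alters neither data collection nor sample size. The downside is that this rare endpoint is no longer adjusted for centre, a randomisation stratum, but so few events could support little such adjustment.

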### Interim analyses {21b}

Not applicable since no interim analyses are planned.

### Methods for additional analyses (e.g. subgroup analyses) {20b}

Descriptive analyses of primary and secondary endpoints will be done within several subgroups of interest to identify potential prognostic and predictive factors. The detailed methodology for all statistical analyses is described in the statistical analysis plan (SAP), which is finalised before database lock. Statistical analysis is performed using SAS v9.4 or higher.

### Methods in analysis to handle protocol non-adherence and any statistical methods to handle missing data {20c}

Missing data for the primary outcome variable due to loss to follow-up or early withdrawal before measurement of the primary endpoint will be replaced by using multiple imputation [33], which takes the covariates treatment group, location (bimaxillary or mandibular osteotomy), and centre into account by application of the fully conditional specification method [29]. This will be realised using the option “FCS” of the SAS “MI” procedure which is implemented in SAS 9.4.

Post-randomisation events will be handled as follows in accordance with the estimands framework. Subjects not undergoing surgery or not receiving at least one dose of postoperative AP or placebo will be excluded, which corresponds to a modified intention-to-treat principle and a principal stratum strategy, as not undergoing surgery or not receiving at least one dose of study treatment is independent of treatment allocation due to the blinded character of the trial. Patients who are lost to follow up or prematurely withdraw their consent before measurement of the primary endpoint will be considered as missing and multiple imputation will be used to impute the primary outcome of these patients, corresponding to a hypothetical strategy. Besides these events, other post-randomisation events will not be considered, thus reflecting a treatment policy approach, which means that the effect of randomised treatment is estimated irrespectively of other post-randomisation events not captured in the primary endpoint definition.

### Plans to give access to the full protocol, participant level-data and statistical code {31c}

The datasets used and/or analysed during the current study can be made available by the corresponding author upon reasonable request and in agreement with the research collaboration and data transfer guidelines of the University of Heidelberg.

## Oversight and monitoring

### Composition of the coordinating centre and trial steering committee {5d}

The steering committee (SC) is comprised of the coordinating investigator and his supporting co-investigators, clinical experts not directly involved in the clinical trial and the responsible biometrician. The SC is responsible for the scientific integrity of the clinical trial protocol, the quality of the clinical trial conduct as well as for the quality of the final clinical trial report. The SC will decide on the recommendations made by the DMC.

### Composition of the data monitoring committee, its role and reporting structure {21a}

A Data Safety Monitoring Board (DSMB) will be set up to monitor safety aspects of the trial and to support the sponsor’s decision-making regarding progress of the trial. The working methods of the committee are based on the guideline EMEA/CHMP/EWP/5872/03 Corr.

The tasks of the DSMB are to ensure the ethical conduct of the trial and to protect the rights and welfare of the involved patients. The DSMB consists of 3 experts representing the field of cranio-, oral and maxillo-facial surgery and statistics. Since the trial is carried out in a double-blind fashion, an external biometrician participates in the DSMB. The DSMB will be regularly informed of all safety aspects of the trial and will review the safety data. A meeting or telephone conference with the board will be scheduled approximately twice a year to review the trial’s progress, to ensure adherence to the protocol, to advise whether to continue, modify, or stop the trial. The DSMB will also assess whether or not the recruitment plan is on target. Based on relevant information from within the trial or from other sources, the DSMB will monitor possible (serious) adverse events and may make a recommendation to the sponsor or to the SC to stop the trial at any time.

### Adverse event reporting and harms {22}

AEs will be ascertained by the investigators using non-leading questions, noted as spontaneously reported by the subjects to the medical staff or observed during any measurements on all clinical trial days. The observational period begins with the first administration of the IMP (day 0, postoperatively) and ends with the visit 8, POD90. However, all AEs observed up to POD90 will be followed up in order to determine their outcome. AEs will be documented in the subject file and in the eCRF. All AEs untoward medical events occurring prior to the beginning of the observational period will be recorded in the eCRF as medical history. All subjects who present AEs, whether considered associated with the use of the clinical trial medication or not, will be monitored by the responsible investigator to determine their outcome. This applies also to subjects who were withdrawn from the clinical trial.

The subjects should report any AEs occurring during the outsubject part to the clinical trial centre by phone.

All SAEs and their relevance for the benefit-risk assessment of the clinical trial will be evaluated continuously during the clinical trial and for the final report. All SAEs will be documented in the “Serious Adverse Event” form and must be reported by the investigator to the delegated Safety Department immediately, but not later than 24 h after the SAE becomes known. All SAEs will be subject to a second assessment by Sponsor’s designated person, who will be independent from the reporting investigator.

Pregnancy itself is not regarded as an adverse event. If a subject becomes pregnant during the course of the clinical trial, the treatment must immediately be discontinued. The outcome of any conception occurring between the first administration and 3 months after the last administration of the IMP will be followed up and documented. If any pregnancy, suspected pregnancy, or positive pregnancy test occurs in the course of the clinical trial, it must immediately be reported to the delegated Safety Department.

### Frequency and plans for auditing trial conduct {23}

Regulatory authorities and/ or auditors authorised by the sponsor may request access to all source documents, eCRFs, and other clinical trial documentation. Direct access to these documents must be guaranteed by the investigator who must provide support at all times for these activities. The investigator will inform the sponsor immediately about a planned inspection.

### Plans for communicating important protocol amendments to relevant parties (e.g. trial participants, ethical committees) {25}

Before the start of the clinical trial, the clinical trial protocol, informed consent document, and any other appropriate documents will be submitted to the independent Ethics Committee (EC) as well as to the competent authority (BfArM).

A written favourable vote of the EC and an (implicit) approval by the competent authority are a prerequisite for initiation of this clinical trial. The statement of EC should contain the title of the clinical trial, the clinical trial code, the clinical trial site, and a list of reviewed documents. It must mention the date on which the decision was made and must be officially signed by a committee member. This documentation must also include a list of members of the EC present on the applicable EC meeting and a GCP compliance statement.

Coordination Centre for Clinical Trials (KKS) Heidelberg who is responsible for submitting the documents will keep a record of all communication with the EC and the regulatory authorities. Before the first subject is enrolled in the clinical trial, all ethical and legal requirements must be met. All planned substantial changes (see §10, [1] of German GCP-Ordinance) will be submitted to the EC and the competent authority (BfArM) in writing as protocol amendments. They have to be signed by the sponsor and biometrician and approved by the EC and the competent authority.

### Dissemination plans {31a}

All information concerning the clinical trial is confidential before publication. Publication(s) and/or presentation(s) of the clinical trial results is encouraged after appropriate time for review and written agreement by the sponsor. The sponsor has to be provided with a draft of the abstract and/or manuscript for review and editorial comments at least 30 days prior to submission and/or presentation. Neither the sponsor nor the Coordinating Investigator has the right to prevent publication, except for patent or copyright purposes. Clinical trial data published or disclosed to third parties must not contain data that allow the identification of a subject.

## Discussion

OS is the surgical correction of a deformity of the jaw. It is a general term that includes several elective surgical techniques to correct facial deformity, the associated malocclusion and functional disorders related to the stomatognathic system [34]. Compared to other surgical procedures, OS are elective, worldwide standardised and therefore reproducible techniques that are usually performed by the same surgical teams, always in a stationary setting. Because the upper digestive tract is penetrated during OS, interventions are classified as clean-contaminated [35] and consequently AP might be mandatory in order to prevent surgical site infection when implant insertions are being performed.

Indeed, the role of bacterial biofilms from the surface of implants (as used for stabilisation of maxillary or mandible osteotomy segments) in the development of local or regional infectious complications is well recognised and has been evaluated in many experimental studies [36]. Some study authors advocate that morbidity can be kept to a minimum with adherence to general surgical principles [8]. Additionally, it is hypothesised that prophylactic antibiotics are of questionable value regarding the prevention of infections, and that their deployment could lead to the development of super infections and stimulate further resistances to antibiotics [1].

Hence, it is discussed whether the use of prophylactic antibiotics may reduce the postoperative infection rates [2]. Therefore, many attempts have been made to determine the efficacy of AP after OS and highly heterogeneous results have led to a plethora of inconsistent recommendations within the literature [4]. Even systematic reviews incorporating meta-analyses focusing on this issue vary in their conclusions [37].

This shortcoming motivated the Cochrane collaboration to perform a systematic review in 2015 including 11 (out of 96 eligible) studies. An overall moderate quality of evidence was identified, thus uncovering the need to perform a RCT in which additional outcomes besides surgical site infections are assessed [4]. However, current prospective RCTs fail Cochrane’s appeal in respect to the study protocol, power estimation, bias and medication chosen [15]. In 2018, a newly performed meta-analysis highlights again this shortcoming and concludes that in the field of OS, most studies of antibiotic prophylaxis are poorly performed and reported [20]. Therefore, scientific uncertainty remains with respect to the necessity, preferred antibiotic compound and optimal range of the prophylaxis.

